## Abstract

**Background:**

It is common for toddlers to display disruptive behaviors (e.g., tantrums, aggression, irritability) but when these become severe and persistent they can be the start of a trajectory towards poor outcomes in childhood and adolescence. Parent Child Interaction Therapy - Toddler is an intervention model designed to meet the specific developmental needs of toddlers aged 12–24 months presenting with disruptive behaviors.

**Methods:**

This study will use a randomized controlled design to evaluate the efficacy of the Parent Child Interaction Therapy - Toddler intervention for children aged 14–24 months with disruptive behaviors. Ninety toddlers with parent-reported disruptive behavior will be randomly allocated to either Parent Child Interaction Therapy - Toddler, Circle of Security– Parenting™ or a waitlist control group. Key parenting capacity outcome variables will include positive and negative parenting, parenting sensitivity, parental sense of competence in managing negative toddler emotions, parent sense of caregiving helplessness, parent mentalizing about the child, parent emotion regulation, child abuse potential and parental stress. Key outcome variables for children will include child social-emotional functioning (initiative, relationship functioning, self-regulation), child emotion regulation, child attachment security, and child behavior.

**Discussion:**

Delivered in the early intervention period of toddlerhood, Parent Child Interaction Therapy - Toddler has the potential to bring about significant and lasting changes for children presenting with early onset behavioral issues.

**Trial registration:**

Australian New Zealand Clinical Trials Registry (ANZCTR), 12618001554257. Registered 24 September 2018 – retrospectively registered.

## Background

Behavioral difficulties in infancy and toddlerhood including persistent tantrums or aggression can signify the start of a trajectory towards poor psychiatric and psychosocial problems across the lifespan [1]. While such behaviors typically represent normal responses to the challenges of the developmental stage and may resolve naturally, evidence suggests that persistent and untreated early onset behavioral difficulties can predict social-emotional challenges, academic problems and conduct disorders in middle childhood and adolescence [2, 3], and psychopathology and anti-social behavior in adulthood [4, 5]. The wider impacts in terms of parental stress [6], added risk for harsh and abusive parenting [7], and social concerns [8], also are also significant and well established.

Although various genetic, social, and temperament pathways to early onset behavioral difficulties have been proposed [9, 10], it is widely agreed that the quality of the early parent-child attachment relationship plays a key role in determining the child’s capacity for behavioral and emotional control [11]. Attachment theory and supporting empirical evidence [12, 13] suggest that when children in the early years of life receive ‘sensitive’ caregiving (defined as a parent’s capacity to notice and correctly interpret the child’s signals, and then to respond appropriately and promptly [14]) - they are more likely to develop a ‘secure’ attachment relationship with the caregiver. Behaviorally, this manifests in the Strange Situation Procedure (SSP) [15] - the well-known experimental paradigm designed to assess attachment patterns in infants - as distress on separation from the caregiver followed by active utilisation of the caregiver on reunion for emotional support. It is thought to be within the context of a safe and supportive attachment relationship that the securely attached child develops the social-emotional skills required for behavioral and emotional control [11], hallmarks of healthy psychological development. In contrast, children who have received insensitive, unresponsive or inconsistent caregiving in their early years tend to develop an alternative strategy to organise their behavior, described as an ‘insecure’ attachment pattern (either avoidance or ambivalence) [15]. Finally, a ‘disorganized’ attachment pattern can also be observed among children who have received parenting with frightened, frightening or dissociative features [16, 17]. Typically observed in the SSP as odd, contradictory, disorganized behaviors in the presence of the parent, this pattern is thought to represent a breakdown or incoherence in the child’s organisational strategy and is known to be associated with the poorest psychological outcomes [17–20]. These theoretical assertions are backed by empirical evidence showing that insecure and disorganized attachment patterns in infancy predict disruptive/externalizing behaviors in later childhood [21].

In seeking to better understand the intergenerational transmission of caregiving quality and attachment, research attention has naturally turned to the investigation of parental factors and characteristics that are associated with, and predictive of, parenting sensitivity and infant attachment security. A parent’s own state-of-mind regarding his or her own attachment history has been identified as one of the strongest predictors of both parental sensitivity and child attachment security [22, 23]; however, other predictors have also been identified. These include parents’ capacity to regulate thier own emotions [24, 25] and their “mentalizing” ability - their ability to keep the child’s ‘mind’ (i.e., thoughts, feelings, intentions, desires) in his or her mind [26–28].

Given the opportunities that early childhood presents for intervention to support and enhance parent-child relationships, a number of attachment-based parenting intervention approaches targeting high-risk children and caregivers have been developed [29]. Examples include Video-feedback Intervention to promote Positive Parenting and Sensitive Discipline (VIPP-SD) [30], Attachment and Biobehavioral Catchup (ABC) [31, 32], and the Circle of Security Intensive Intervention (COS-I) [33]. Each of these interventions aims to address parenting sensitivity and some explicitly target infant attachment and disruptive/externalizing child behaviors. Evidence for the efficacy of these programs in relation to the specific age of toddlerhood (12–24 months) and for reducing disruptive child behaviors, however, is limited and equivocal. VIPP-SD [30] involves review of video-taped parent-child interaction sessions in the home and aims to increase parental sensitivity and sensitive parental discipline, defined as the ability to take into account the child’s perspective and signals when discipline is required. VIPP-SD has been shown to be effective in enhancing maternal attitudes toward sensitivity and sensitive discipline and in promoting sensitive discipline interactions. The intervention also resulted in decreased overactive problem behaviors, but only among children in families with elevated levels of marital discord and daily hassles (e.g., money problems or troubles at work); child externalizing behaviors remained unchanged. ABC is based around active coaching of the parent from a therapist in ten 1-h home-based sessions, with coaching focused specifically on enhancing nurturance of the child, following the child’s lead with delight, and reducing frightening/intrusive behavior. ABC has been shown to be associated with a range of positive outcomes including decreased rates of disorganized attachment and increased rates of secure attachment [34], normalized diurnal cortisol production in children [35], enhanced child executive functioning [36], and improved emotion expression [37]. The efficacy of the program for disruptive or externalizing behavior in the toddler age group, however, has not been specifically demonstrated. COS-I comprises a mix of individual and group components spread over 20 weeks, and aims to increase caregiver sensitivity and responsiveness to child cues, empathy for the child by supporting parental reflective functioning, recognition and understanding of child attachment cues, and awareness of the impact of the caregiver’s own attachment history on caregiving. COS-I has not yet been evaluated using a RCT but open trial designs suggest positive changes in terms of child attachment security, internalizing and externalizing symptoms, and in parenting stress and parent mood problems [38–41]. Given the wide age range in these studies (1–8 years), specific outcomes for toddlers aged less than 2 years are unknown. Taken together, it is clear that there is a need for new intervention models to address the unique needs of parents and toddlers in the 12–24 age range experiencing early onset disruptive or externalizing behaviors.

‘Parent Child Interaction Therapy – Toddler’ (PCIT-T) [42] is a new parenting intervention program designed to address behavioral problems in young toddlers aged 12–24 months. Drawing on both attachment and social learning theories, and grounded in developmental principles, PCIT-T assumes that (i) problematic behaviors in young toddlers indicate emotional dysregulation rather than deliberate, intentional attention-seeking acts or components of a coercive parent-child interaction cycle, (ii) the early parent-child attachment relationship is the vehicle through which capacities for emotion and behavior regulation in the young child emerge and are consolidated, and (iii) young toddlers have the capacity to learn new skills. The program aims to improve basic parenting skills (e.g., increase use of praise and reduce negative language directed at the child), to increase the parent’s awareness of, and sensitivity to, the child’s emotional experience and needs, to improve the parent’s capacity to support the child’s emotional regulation, to improve the parent’s own emotional regulation skills, and to improve the child’s listening skills and compliance. Through improvements in these domains, it is expected that infant attachment security, child social emotional functioning including emotion regulation, and externalizing behaviors, will be natural flow-on effects. PCIT-T is an adaptation of standard PCIT [43], developed for children aged 2–7 years presenting with conduct problems. Full descriptions of standard PCIT and overviews of the evidence base can be found elsewhere [43, 44]. Although there are some shared features between standard PCIT and PCIT-T, PCIT-T differs significantly from standard PCIT in its explicit emphasis on emotion regulation for both child and parent, and lack of a formal ‘discipline’ phase or time out procedure.

As is the case in standard PCIT, the PCIT-T program utilizes in-clinic parent-child play sessions with direct live coaching from the therapist, usually from behind a one-way mirror using a bluetooth in-ear microphone. There are two phases of the program, ‘Child Directed Interaction - Toddlers’ (CDI-T) and ‘Parent Directed Interaction-Toddlers’ (PDI-T). The CDI-T phase teaches parents to (a) use ‘P-R-I-D-E’ skills (labeled Praise, Reflections of child verbalizations, Imitating child play, Behavioral Descriptions, and Enjoyment); (b) reduce ‘Don’t behaviors’ (avoiding questions, commands and criticisms); and (c) use ‘C-A-R-E-S’ techniques to help the child regulate emotions when needed (Coming in close, Assisting the child, Reassuring the child, Labeling the Emotion, Soothing the child). In the CDI-T phase the parent is also taught to use “under-reaction and re-direction” in response to disruptive child behavior judged to be attention seeking (e.g., throwing toys) and to use a brief, developmentally appropriate limit-setting sequence in response to child aggression. The limit-setting sequence involves the parent coming close to the child, taking his or her hands, and, with direct eye contact, saying, “no hurting”. The parent then looks away for 3 s, and then looks back at the child and says, “no hurting, gentle hands” before rotating the child towards the toys and using PRIDE skills (and CARES skills, where needed) to re-engage the child in positive play. The PDI-T phase aims to promote toddler listening skills through a fun, game-like, guided compliance teaching sequence. Throughout both phases, to enhance parents’ ability to effectively implement the CDI-T and PDI-T skills, parents are also encouraged to develop their own emotion regulation skills through application of a parallel adult-focused C-A-R-E-S model [Coming in close to your own feelings, Assisting yourself to manage (e.g., deep breathing, progressive muscle relaxation), Reassuring yourself (cognitive challenging), Labeling Emotions experienced, Soothing yourself (e.g., self care)]. Between PCIT-T sessions, parents are encouraged to practice the skills with the child for 5 min on a daily basis. All sessions begin with a brief “check in” conversation in which the therapist and parent discuss and problem-solve any issues around home practice, and reflect on the parent’s experiences using the PRIDE and CARES skills (for both themselves and the child) during the week. Following the “check in”, the therapist observes the parent and child for 5 min (without providing coaching), and in this time codes the parent’s use of the PCIT-T skills (e.g., PRIDE skills, Don’t behaviors, CARES techniques). This allows the therapist to choose a focus area for the session and to track progress across sessions. The PCIT-T program is mastery-based, meaning that parent-child dyads progress from the CDI-T phase to the PDI-T phase when they show satisfactory use of the CDI-T skills in the 5 min observational period (i.e., they are observed to use 10 labeled praises, 10 behavioral descriptions and 10 reflections, and to adequately implement the CARES skills when needed). Graduation from the PDI-T phase takes place when the parent can competently implement the guided compliance teaching sequence. For most dyads, when PCIT-T is delivered twice weekly (30–40 min per session), CDI-T and PDI-T mastery is typically achieved after approximately 10–12 sessions.

Preliminary evidence to support the efficacy of PCIT-T has been positive. Kohlhoff and Morgan [45] initially made adaptations to the standard PCIT protocol including greater emphasis on preventing problem child behavior by increasing focus on the creation of safe, developmentally appropriate environments, and early intervention in the case of emotion dysregulation. There was no PDI phase but some developmentally appropriate limit setting was integrated into the CDI phase. Redirection was used as a primary form of behavior management, and parent-focused psychoeducation of developmentally appropriate expectations was infused throughout the treatment. Although the behavioral parent-training lens primarily used in PCIT remained at the core of many PCIT-T skills, an attachment-based emphasis on meeting the emotional and developmental needs of toddlers was a key focus of the treatment. Kohlhoff and Morgan [45] retrospectively reviewed outcomes of the first 29 cases treated with this early version of PCIT-T and showed that toddlers who received PCIT-T showed statistically and clinically significant improvements in child behavior and that their parents reported feeling less depressed. Kohlhoff and Morgan [46] subsequently reported results from a study in which mother-child dyads (*n* = 66) participated in a randomized controlled trial (RCT) study to evaluate outcomes of the CDI-T phase of the PCIT-T intervention versus a wait-list controlled condition. Results showed that parent-child dyads who received PCIT-T showed significantly greater gains in terms of increases in positive parenting skills, decreases in negative parenting behaviors, enhanced emotional availability including sensitivity, and reduced child externalizing behavior. When the sample was followed up 4-months after the completion of PCIT-T treatment, parent and child gains after PCIT-T were maintained [47]. The sample size at follow-up was small for categorical analyses, but there was a pattern of positive change from disorganized to organized infant attachment. A sub-sample of study participants also took part in a qualitative interview following treatment completion, and results indicated a high level of consumer satisfaction with the program [48].

The PCIT-T outcome research to date has been limited by the lack of a comparison intervention, no control group at follow-up and the limited range of outcome measures utilized (e.g. no measures of emotion regulation or parental representations) to enable greater understanding of the processes through which child behavior are achieved. There has also been no formal evaluation of the most recent version of the treatment model as articulated by Girard, Wallace, Kohlhoff, Morgan and McNeil [42], which includes structured handouts and record forms for parents, formalized implementation of the adult and child ‘CARES’ models for emotion regulation, and addition of the PDI-T phase for promotion of toddler listening skills and parental provision of effective commands.

### Study aims and hypotheses

The objective of the current study is to evaluate the most recent iteration of the PCIT-T model, as articulated by Girard and colleagues [42]. Study aims will be to 1) examine whether the PCIT-T intervention leads to positive changes in parenting capacity for parents of young toddlers presenting with early disruptive behaviors; and 2) examine social-emotional, attachment and behavioral outcomes for children who participate in PCIT-T.

Three conditions will be tested: a waitlist control group who are not treated, PCIT-T and a group receiving Circle of Security – Parenting™ (COS-P), a group-based attachment-informed preventative parenting education program. COS-P was chosen as the comparison intervention because it is currently delivered as the parenting treatment of choice in many government and community-based settings across Australia [49] and is of a similar treatment length (8 weeks). It is acknowledged that COS-P is not a perfect comparator as PCIT-T is delivered individually while COS-P is delivered to groups of 6–8 participants. To address this, the treatments will be matched for treatment length (8 weeks) and total treatment time (16 h), and study results will be interpreted with the different delivery modalities in mind.

We expect that of the two interventions, PCIT-T will be associated with the greatest treatment gains for the following reasons: (i) PCIT-T is the more intensive treatment model (PCIT-T is delivered on an individual basis; COS-P is a group program), (ii) PCIT-T is targeted at a narrower age range and is therefore more developmentally tailored (PCIT-T is for children aged 12–24 months; COS-P does not specify a child age range), (iii) PCIT-T is designed specifically for children with clinically significant disruptive behaviors and COS-P is not, and (iii) compared to COS-P, PCIT-T has an explicit behavioral component, which aligns with meta-analytic findings indicating that interventions that are brief, have a behavioral component, and which enhance parental sensitivity are most likely to bring about lasting improvements in children’s attachment security and thus capacity for behavioral and emotional regulation [50].

We thus hypothesize that from baseline (‘Time 1’) to post-treatment/waitlist (‘Time 2’) there will be a gradient effect, whereby parent-child dyads who receive PCIT-T will show the greatest gains and parent-child dyads who receive no treatment will show the least gains with respect to the following variables:
Improved parenting capacity through increased i) labeled praise of the child, ii) parenting sensitivity, iii) parent sense of competence in managing negative toddler emotions, iv) parent mentalizing about the child, and v) parent emotion regulation; and decreased i) negative statements directed toward the child, ii) parent sense of caregiving helplessness, iii) child abuse potential, and iv) parental stress.Improved child outcomes including increased: i) emotion regulation maturity; ii) social-emotional functioning including initiative, relationship functioning and self-regulation, iii) attachment security, and iv) decreased externalizing behavior.

Second, we expect that for the two active treatment conditions, this gradient effect will be maintained at a 4-month post-treatment follow-up, whereby parent-child dyads that receive PCIT-T will show superior outcomes on all variables compared to parent-child dyads where the parent received COS-P.

## Methods

### Design

This study will be a RCT comparing outcomes for participants receiving one of two treatment conditions (PCIT-T, COS-P) and those receiving no treatment (waitlist condition).

### Participants and setting

Participants will be 90 toddlers aged 14–24 months with behavioral difficulties referred by a health professional (e.g., General Practitioner (GP), Paediatrician, Early Childhood Nurse, Psychologist) to the Karitane Toddler Clinic (KTC), a specialized outpatient child treatment clinic located in South Western Sydney, Australia. A decision was made to include children aged 14 months and over, rather than the 12 months and over that the PCIT-T intervention is designed for, to increase the likelihood that children in the sample are of a similar developmental stage (e.g., walking, starting to talk) at the time of participation. The study will be advertised using posters and flyers placed in the waiting rooms of GP and Early Childhood Clinics, and online (e.g. advertisements on parenting websites, Facebook and other social media platforms).

### Procedure

#### Recruitment

After being referred to the KTC, families will be informed about the research study and will undergo a clinical intake procedure including (i) an initial phone-based intake interview conducted by an Intake Officer, (ii) a 20-min in-depth phone-based intake assessment conducted by a member of the clinical research team, and, (iii) for complex cases, case review at a weekly multidisciplinary team meeting. A member of the clinical research team will then phone the families who appear suitable for the KTC service to schedule an initial face-to-face clinical assessment session. To be included in the study, the family must have a child aged 14–24 months, a referral from a health professional, and the parent must give a positive response to one or both of two screening questions (‘Do you have concerns about your child’s behavior?’ and/or ‘Do you have difficulties managing your child’s behavior?’). No other screening questions or measures will be used to assess eligibility, however families will be excluded from the study if there is evidence (in the information obtained in the referral or intake assessment) of severe parental depression with suicidality or other serious mental health conditions causing significant impairment in cognition or behaviors (e.g., psychosis) or if they are not sufficiently proficient in speaking English to complete study measures and protocols. Parents will be told that the study seeks to test different approaches to helping parents who are struggling with challenging toddler behaviour. Eligible and willing parents will provide written, informed consent to participate in the research during the first face-to-face assessment session at the KTC.

#### Randomization

Participants who meet the study inclusion criteria will be randomly assigned to receive one of the three conditions using restricted block randomization, using block sizes of *n* = 6. This means that within each block of *n* = 6, 2 participants will be allocated to the PCIT-T condition, 2 participants will be allocated to the COS-P condition and 2 participants will be allocated to the Waitlist condition. The order will be randomized within each block. Figure 1 shows the way that participants will flow through the three assessment points for the study (Time 1, T1; Time 2, T2; Time 3; T3). Randomization will occur at the start of the first face-to-face assessment session (T1), with allocations pulled out of pre-prepared sealed envelopes, but the research team and family will not be informed of the condition to which they have been allocated until after completion of the entire T1 assessment.

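### A single, published block size of 6 at one clinic with open arms lets up to one allocation in five be deduced in advance; varying, undisclosed block sizes would be a cheap improvement

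*Protocol article*

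**What the plan says.** Under Randomization, the protocol article has families "randomly assigned to receive one of the three conditions using restricted block randomization, using block sizes of" six. Within each block, "2 participants will be allocated to the PCIT-T condition, 2 participants will be allocated to the COS-P condition" and the other two go to the waitlist. It adds: "The order will be randomized within each block". No second block size, random variation of size or stratification is described.

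The same section gives two safeguards. Allocations come from sealed envelopes prepared beforehand and drawn at the start of the first T1 session. Neither the team nor the family learns the result until the whole T1 assessment is finished. The section on the Time 1 assessment spreads T1 over three sessions within one week.

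The setting is a single service, "a specialized outpatient child treatment clinic located in South Western Sydney, Australia". The target is given as "Participants will be 90 toddlers aged 14–24 months with behavioral difficulties".

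Under Recruitment, intake includes "a 20-min in-depth phone-based intake assessment conducted by a member of the clinical research team", and then "A member of the clinical research team will then phone the families who appear suitable for the KTC service" to book the first session. Exclusions for serious parental mental illness and for insufficient English rest on information from referral and intake.

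The Interventions section describes individual coaching, group sessions or eight weeks without treatment. The Measures section masks the coders of observational tasks and no one else.

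**The concern.** A constant block size lets past allocations reveal future ones. When both places of two arms have been used, what is left of the block is known. When both places of one arm have been used, that arm cannot come next. The envelope and the delayed disclosure protect a family's own allocation while its T1 is under way. They do not protect the allocations of earlier families in the block, which the team learns about a week after each draw.

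The people who learn those arms belong to the team that conducts the in-depth intake call and books first sessions. If they can narrow the next arm, the order of booking or the handling of a borderline exclusion could follow it, even without intent. A motive is plausible because the section on aims and hypotheses states that PCIT-T is expected to do best. Masked coding does not help here, since it acts after enrolment. Several outcomes are also parent-reported, including the CBCL externalizing score used for the power calculation. Modelling T1 values would deal with part of any imbalance in measured characteristics, but not with unmeasured differences in who was enrolled.

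**Working it through.** **Inputs from the protocol article.** Block size 6, split 2:2:2; 90 families; one clinic, hence one list (no stratification is described); T1 lasting about one week, with disclosure at its end. **Assumed, because the article does not give it:** accrual of 0.25 to 2 families per week, with random (Poisson) arrivals.

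**The plan's own figures.** 90 / 6 = 15 blocks, and 15 × 2 = 30 per arm, which matches the 30 per group in the sample size section. The article states no predictability figure.

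**Ceiling: block boundary and all earlier allocations in the block known.** There are 6! / (2! 2! 2!) = 90 equally likely orders. With r places left, the chance that all belong to one arm is 3 × C(2, r) / C(6, r):
- r = 2 (fifth place): 3 × 1 / 15 = 1/5
- r = 1 (sixth place): 3 × 2 / 6 = 1
- r = 3 or more: 0

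Enumerating the 90 orders gives, by place:

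| Place in block | 1 | 2 | 3 | 4 | 5 | 6 | Sum |
|---|---|---|---|---|---|---|---|
| Arm certain | 0 | 0 | 0 | 0 | 0.20 | 1 | 1.2 |
| At least one arm ruled out | 0 | 0 | 0.20 | 0.60 | 1 | 1 | 2.8 |
| Best guess correct | 0.333 | 0.400 | 0.500 | 0.533 | 0.600 | 1 | 3.367 |

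- Certain: 1.2 × 15 = 18 of 90, or 20%.
- At least one arm ruled out: 2.8 × 15 = 42 of 90, or 46.7%.
- Best guess: 3.367 / 6 = 56.1%, against 33.3% by chance.

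**Effect of delayed disclosure.** The same counts were simulated with an earlier allocation treated as known only after the lag has passed:

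| Accrual (assumed) | Lag | Certain, of 90 | Arm ruled out, of 90 | Best guess |
|---|---|---|---|---|
| 0.25/week | 1 week | about 15 | about 38 | 53–54% |
| 0.5/week | 1 week | about 12 | about 34 | 51% |
| 1/week | 1 week | about 8 | about 28 | 48% |
| 2/week | 1 week | about 3 | about 17 | 42% |
| 1/week | 2 weeks | about 3 | about 16–17 | 42% |
| 2/week | 2 weeks | under 1 | about 5 | 37% |

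The two-week rows matter because booking by telephone precedes the draw, so the lag that applies at booking is longer than one week.

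**Effect of varying block sizes.** Sequences of 90 were simulated for a guesser who knows every earlier allocation and the set of possible sizes, but not which size was drawn:

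| Block sizes | Certain, of 90 | Arm ruled out, of 90 | Best guess |
|---|---|---|---|
| 6 only | 18 | 42 | 56% |
| 6 or 9 | about 4.6 | about 12.4 | 54% |
| 6, 9 or 12 | about 2 | about 6 | 53% |

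A larger fixed block would help much less. The certain share would be 14.3% with blocks of 9 and 11.1% with blocks of 12.

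**The case against.** A reader might infer that one allocation in five is simply predictable under this plan. The documents do not support that. The figure needs every earlier family in the block to have been disclosed, and the block boundary to be known, before the next family is booked. The plan withholds each arm until T1 is complete, and at faster accrual this shrinks the figure to a few percent.

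The document even hints at faster accrual. COS-P runs in groups of 6 to 8, and treatment should start as soon as possible. Filling one group from trial families alone takes about 3 × 6 = 18 to 3 × 8 = 24 randomizations; over an assumed 4 to 8 weeks, that is 18 / 8 = 2.25 to 24 / 4 = 6 families per week. At 3 per week with a one-week lag, only about 1.4% of allocations are certain. This argument has weight but does not settle the matter, because the article does not say whether the groups also take families from outside the trial.

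A reader might also take the telephone selection of suitable families as a judgement of trial eligibility. The text concerns suitability for the clinic's service. Trial inclusion is nearly mechanical: age, referral, and a positive answer to at least one of two questions. Some judgement remains in the exclusions and in the order of booking, but the room for it is narrow, and intake is shared with an intake officer and, for complex cases, a team meeting.

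Finally, a reader might infer that the envelopes were prepared or held by the recruiting team. The article is silent on this. A full protocol commonly covers it, so it cannot be counted as a fault.

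**Conclusion.** The point holds as a modest weakness in a stated design choice. The article contradicts nothing here, and it gives no evidence that steering occurred. With one fixed and published block size, up to 18 of 90 allocations can be deduced and up to 42 of 90 can have an arm ruled out. The delay to the end of T1 reduces this without removing it: to roughly 15 down to 3 certain, and 38 down to 17 with an arm ruled out, for a one-week lag and 0.25 to 2 families per week. A longer lag or faster accrual makes it smaller still.

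The ceilings rest on exact enumeration. The reduced figures rest on an assumed accrual rate, and on an observer who knows the block boundary and keeps track of disclosed allocations. Whether intake staff do so is not stated.

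**What to change.** Generate the remaining allocation list with block sizes drawn at random from multiples of 3, for example 6, 9 and 12, starting at the next block boundary. Keep the sizes out of anything recruiting staff see. Keep the sealed envelopes and the delayed disclosure as they are.

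The gain lies almost entirely in certain and ruled-out allocations. Best-guess success barely moves, because any scheme that keeps the arms balanced leaves some information in past allocations.

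The cost is preparing new envelopes for the families still to be randomized. The analysis and the sample size do not change. Arm sizes may end slightly unequal if recruitment stops inside a block: by at most 4 between any two arms with a largest block of 12, since 12 / 3 = 4.
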